##### Data collection

To track all the activities associated with a D&I strategy and BHF program online training, recruitment and delivery, we use a publicly available time-tracking tool (i.e., Clockify), which is accessible through the website or smartphone app, to monitor the activities logging in by the community facilitators or the research team. To mitigate the potential respondent burden, we pre-populate the identified implementation activities associated with each D&I strategy proposed in the trial on the Clockify platform. Community facilitators in both conditions will be asked to record their BHF associated activities if any (typically the day before and the day of the BHF sessions) using either the web- or mobile-based Clockify app. They will receive weekly reminders for weekly implementation activity tracking, regardless of their group assignment, through an automated system email sent out during the weekend. In addition, the project coordinator will engage with the communities for reminders via emails, text messages, or phone calls if any given data was not logged in the system. We will supplement the cost data collection with meeting attendance sheets and minutes (for the research team and CAB members) and a BHF session check-in sheet (for participants).

##### Data analysis

Table 1 summarizes the proposed within-trial economic evaluation and associated costs and outcomes by the RE-AIM indicators. The cost-effectiveness of D&I strategies is assessed by combing their associated costs and outcomes using an incremental implementation cost-effectiveness ratio [33] (ICER) if a strategy is simply applied to the BHF-LC with the BHF-PO as the comparison group or average implementation cost-effectiveness ratio [34] (ACER) if a D&I strategy is applied in both the BHF-LC and BHF-PO conditions (and thus no comparison group). The interpretation is similar to the interpretation for a trationdtional ICER. An ICER is interpreted as the extra cost incurred for the intervention to achieve an extra 1 unit of increase in outcomes (reach, adoption, implementation, and maintenance) measured, whereas ACER represents the cost associated with a one-unit change on given measures for the outcome of interest. For example, the ACER for the fund and contract dissemination strategy to increase the adoption of the BHF program, at the micropolitan and surrounding rural areas is described as the costs associated with one community responding to RFA and contracted to implement BHF.

Similarly, the cost-effectiveness of the BHF program is determined by the total LC costs (BHF-LC group only) and the BHF program costs consisting of training, recruitment, program delivery, and post-follow-up, and the effect of BMI *z*-score reduction at 6 and 12 months. The ICER result is interpreted as the cost for an additional unit decrease in BMI *z*-scores between the BHF-LC and BHF-PO conditions.

To ascertain whether a given ICER/ACER is cost-effective, we will compare them to thresholds that are based on findings from previous economic research [13].

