Despite the proposed promise of these approaches, it is necessary to understand both the ability of these strategies to improve RE-AIM outcomes as well as the costs and resources needed to execute D&I strategies [10–12]. Unfortunately, study findings from those that have conducted economic evaluations of D&I strategies are mixed and thus the economic feasibility of D&I strategy use remain unclear. In studies that have applied economic analysis of LCs [13, 14], a cost-effectiveness analysis (CEA) focusing on pre-post changes in clinician’s competency on trauma-focused cognitive behavioral therapy and youth’s trauma-related mental health found the LC did not produce a favorable cost-effectiveness ratio with clinician competency as the outcomes measure. However, the subsequent reductions in youth psychopathology demonstrated a high cost-effectiveness. More broadly, two recent review studies [15, 16] identified articles examining the costs, consequences, and cost-effectiveness of strategies designed to influence the adoption of public or population-level interventions in community settings. Both reviews shared the methodology limitation that the number of studies that they identified and synthesized, especially among studies associated with the implementation or implementation strategies, and a plethora of terms and definitions of D&I strategies making cross-study comparisons related to CEA challenging. Moreover, no detailed discussion of costing methods was found in their reviews.

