##### Non-labor costs

Non-labor costs include gym and classroom space, scales, diet books, printouts, handouts, educational supplies, equipment, and financial incentives provided for BHF participants and will be collected based on actual amounts spent and tracked from receipts and paid invoices. Costs of computers, Internet, and landline will not be included given that they are provided to community facilitators to conduct their daily tasks. To supplement the cost estimate of D&I strategies, we will also obtain cost information during the exit interview of community facilitators, as suggested by the literature [14].

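### One cited source supplies the cost-effectiveness thresholds for every ratio, but the outcomes described for it match none of the seven Table 1 units, and two of the ratios are averages with no comparator

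*Protocol article*

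**What the plan says.** The Data analysis section of the protocol article sets one decision rule for ratios of either kind: "we will compare them to thresholds that are based on findings from previous economic research [13". No outcome is exempted and no other source is named. The same section reserves the ICER for strategies given only to the learning collaborative (LC) communities. It uses the ACER where both conditions receive the strategy, and states that nothing is then available to compare against.

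The only other mention of reference 13 is in the Background, in a sentence that begins "In studies that have applied economic analysis of LCs [13, 14], a cost-effectiveness analysis (CEA) focusing on pre-post changes". Two measures are named there: how skilled clinicians became in a trauma-focused therapy, and the mental health of the young people they treated. For the first, the article reports that "the LC did not produce a favorable cost-effectiveness ratio with clinician competency as the outcomes measure". For the second it reports the opposite picture, namely that "the subsequent reductions in youth psychopathology demonstrated a high cost-effectiveness".

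Table 1 lists seven ratio rows with their interpretations. Five are ICERs and two, marked C_all/E_all, are ACERs. The Sensitivity analysis section adds a cost-effectiveness analysis on parents' weight loss.

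**The concern.** A cost-effectiveness threshold is an amount of money per unit of a particular outcome. The article applies one threshold source to ratios with several different denominators, and the outcomes it reports from that literature are not among them. It also puts average ratios to the same test as incremental ones, although an average ratio does not measure extra cost for extra effect.

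At stake are the labels attached to the results. Followed as written, the rule would call strategies cost-effective or not without a criterion that fits the ratio being judged. The Background and the Conclusion both expect payers, policymakers and communities to draw on these results.

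**Working it through.** The documents give no threshold value, willingness-to-pay figure or expected ratio, so there is no figure to reproduce. The check sets units side by side.

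**Step 1. Units of the ratios (Table 1) against the outcomes described in the Background.**

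| Table 1 row | Type | Ratio is in dollars per | Match with clinician competency or youth psychopathology |
|---|---|---|---|
| Reach | ICER | extra person recruited | none |
| Effectiveness | ICER | unit of BMI z-score reduction | none (a child health outcome, but a different measure) |
| Adoption, fund and contract | ACER | adopting community | none |
| Adoption, cohorts | ICER | extra cohort started | none |
| Implementation, LC | ICER | change in fidelity score | related concept, different scale |
| Implementation, package | ACER | knowledge score or fidelity unit | related concept, different scale |
| Maintenance | ICER | extra third cohort | none |

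Count: 1 + 1 + 2 + 2 + 1 = 7 rows, of which 5 are ICERs and 2 are ACERs. Rows sharing a unit with the described analysis: 0 of 7. Two rows are related in concept, because the Effect measurement section treats the knowledge check as a measure of facilitator competence. The other five have no counterpart in the same unit. The parents' weight-loss analysis does not match either.

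**Step 2. Why the unit decides.** For outcome k, an ICER ΔC/ΔE_k with ΔC and ΔE_k both positive passes if it is at most λ_k, which is the same as net benefit λ_k·ΔE_k − ΔC ≥ 0. λ_k is in dollars per unit of k. A value of λ for competency cannot be multiplied by a change in BMI z-score or a count of cohorts. A related concept does not solve this: multiplying a fidelity or knowledge scale by a constant a divides the ratio by a, with no change in the programme, so a threshold from another instrument has no fixed meaning on it. The Background shows the same dependence: the LC was judged unfavourably on one outcome and favourably on another.

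**Step 3. Could a generic threshold be meant?** A generic health threshold needs a common outcome such as a QALY, or a mapping to one. The article has neither.

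**Step 4. The two average ratios.** C_all/E_all equals an incremental ratio only against an alternative with zero cost and zero effect: C/E = (C − 0)/(E − 0). If the effect without the strategy is E₀ = f·E with 0 < f < 1, and cost without it is still zero, the incremental ratio is C/(E − E₀) = (C/E)·1/(1 − f). The ACER then understates the incremental cost per unit by the factor 1/(1 − f). The article gives no f, and by design has no group from which to estimate it. This step does not depend on what reference 13 contains.

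**The case against.** The strongest reply is that reference 13 is not in view. The rule speaks of thresholds based on that work's findings, which leaves room for derived or generic values, and an LC economic study is not an arbitrary source for an LC trial. Outcome-specific figures may also be left to a fuller plan. This stands in part: the absence of numbers is not the point here. The point is that the article itself chooses one source for all ratios, while what it reports of that source fits none of them and no bridge is stated.

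A reader might infer that reference 13 is the trauma-therapy study. The Background cites 13 and 14 together and does not say which one it describes. The separate use of 14 for exit-interview costing ("as suggested by the literature [14") does not settle it.

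A reader might also infer that the outcomes are wholly unrelated, or that no ratio here could ever be classified. Neither is supported. Facilitator competence is close to clinician competency as a concept, and an ICER that is dominant or dominated needs no threshold.

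On the average ratios, a zero baseline is a plausible assumption for communities contracted under fund and contract, and much less so for knowledge or fidelity scores. But the article does not state that assumption, and even with it a threshold in dollars per contracted community would be needed.

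Finally, the Challenges and limitations section calls this a pilot economic evaluation and says that use of the cost evaluations by decision makers is not addressed. That limits the consequence. It does not withdraw the planned verdict, and it sits uneasily with the Background and Conclusion.

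**Conclusion.** The concern holds in this form: the article supplies no usable threshold for its own ratios. None of the seven Table 1 rows is in the units of the only analysis it describes from the cited literature, and two of the seven are average ratios for which an incremental threshold cannot support a cost-effective verdict.

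The unit finding rests on the article's own account of references 13 and 14 taken jointly, and would need revisiting if reference 13 proves to give thresholds in these outcome units or a stated mapping to them. The average-ratio finding rests only on the article's own definition of the ACER. The costs, effects and ratios themselves are not affected, only the labels put on them. The point should be corrected, but it does not undermine the evaluation.

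**What to change.** In the Data analysis section, replace the single-source threshold comparison as follows.

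- **ACERs (two rows):** report cost per unit descriptively, with no cost-effective verdict.
- **ICERs (five rows):** either justify a threshold in each outcome's own unit and say how it was derived, or report incremental cost and incremental effect with net benefit or acceptability over a stated willingness-to-pay range. State dominance where it occurs.

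For BMI z-score, the 2000 bootstrap cost-effect pairs already planned can supply an acceptability curve. For outcomes measured at community level the comparison is four communities against three, so net benefit over the range should be presented as descriptive.

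The cost is a change of wording and one extra plot, with no new data. What is given up is a yes/no label that the article's stated source, as described there, does not support.

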##### Sensitivity analysis

Performing a sensitivity analysis is a critical component of an economic evaluation when the assumptions and parameter estimates applied in the analysis have uncertain precision. Two approaches will be employed in the proposed economic evaluation. The first approach is one-way deterministic sensitivity analysis (DSA) [35] for the cost analysis of D&I strategies and BHF program training, recruitment and delivery. We will conduct the DSA around key unit costs, cost components, and outcome measures (i.e., BMI *z*-score) to assess the impact of these changes/variations on the total costs and cost-effectiveness [36, 37]. We will use tornado diagrams to summarize the effects of varying key input parameters one at a time on the results of the ICER/ACER [38]. Parameters to be considered include but are not limited to the role and salary level of key personnel, intensity/number of BHF sessions, and changes in the lengths of attendance time for the session. The parameters will be sorted in descending order by their influence on the ICER/ACER. The longer bars indicate the most important parameters. The second approach is a nonparametric bootstrap simulation, and it will be used to construct the joint uncertainty (e.g., 95% confidence interval) for the incremental costs and incremental effects (i.e., BMI *z*-score reduction) between BHF-LC and BHF-PO conditions. In the bootstrap simulation, 2000 random samples of cost-effect pairs will be selected with replacement from the original trial dataset. Simulation results will be presented graphically using a scatter plot (i.e., the incremental cost-effectiveness plane [ICEP]) [39], where each dot represents the ICER of one iteration of the bootstrap simulation. In addition, we will conduct CEA of BHF intervention using parents’ weight loss outcomes at 6 and 12 months. Moreover, we will conduct scenario analyses under different settings and conditions to estimate replication costs to enhance decision-making for potential adopting communities [40, 41].

All analyses will be performed using Stata 16.0 (StataCorp LP, College Station, TX) or Microsoft Excel.

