## Methods

### Study design

This economic evaluation protocol is embedded within a type III HEI trial, aiming to test multilevel D&I strategies that focus on the RE-AIM outcomes of an evidence-based PWMI (i.e., Building Health Families [BHF] [20–22]). Details of the overarching trial have been published elsewhere [3, 5, 23] and information on that trial is presented here as it relates to the economic evaluation of strategies that target RE-AIM outcomes (see Table 1). Specifically, the trial includes three primary D&I strategies—fund and contract, an online, packaged implementation blueprint, and an action LC. In addition, the implementation blueprint includes activities focused on training, program implementation, and referral resources to improve program reach. Similarly, the LC includes activities focused on network weaving, used to promote information sharing within and outside the organizations building upon existing working relationships [6], consultee-centered training, and sustainability action planning. The study is intended to (1) identify local demand for BHF, a PWMI that was used as the basis for the online, packaged implementation blueprint (referred to hereafter as the BHF Online Training Resources and Program Package [5]); (2) examine potential determinants of BHF adoption; and (3) compare BHF RE-AIM outcomes in communities that participate in the LC to those that do not. As a pilot type III HEI, the primary aim is to determine if the LC communities document better D&I outcomes (reach, adoption, implementation, BHF sustainability) and the secondary aim is to determine the relative effectiveness of BHF between communities that participate in the LC versus those that do not. Of note, regardless of LC participation status, communities are exposed to strategies of fund and contract and BHF Online Training Resources and Program Package. The trial protocol is registered with clinicaltrials.gov (NCT04719442).

**Table 1 Tab1:** Cost and outcome measures for the within-trial economic evaluation by the RE-AIM outcomes

Outcomes	Corresponding strategy	Cost of BHF-LC (C_**LC**_)	Cost of BHF-PO (C_**PO**_)	Outcome measure (E)	ACER/ICER	Interpretation

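### The tornado ranks parameters by ICER bar length while varying BMI z-score; if the between-arm effect difference reaches or crosses zero, bar length no longer measures influence and the ranking can be wrong

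*Protocol article*

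**What the plan says.** Three statements in the Sensitivity analysis section combine into one rule.

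- What is varied: "We will conduct the DSA around key unit costs, cost components, and outcome measures", with BMI z-score given as the outcome measure.
- What is plotted: "We will use tornado diagrams to summarize the effects of varying key input parameters one at a time on the results of the ICER/ACER".
- How it is ranked and read: "The parameters will be sorted in descending order by their influence on the ICER/ACER", followed by "The longer bars indicate the most important parameters".

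Table 1 gives the effectiveness ratio as the cost difference between BHF-LC and BHF-PO over the difference in their outcomes. The Data analysis section agrees: "The ICER result is interpreted as the cost for an additional unit decrease in BMI *z*-scores between the BHF-LC and BHF-PO conditions". On what separates the arms, the Study design section notes that "regardless of LC participation status, communities are exposed to strategies of fund and contract and BHF Online Training Resources and Program Package". The Community level section allocates four communities to BHF-LC and three to BHF-PO.

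The article gives no range for the z-score variation and no expected effect. It does not say how a zero or negative effect difference would be shown.

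**The concern.** Bar length is a fair measure of influence only when the plotted result moves steadily in one direction as the input moves. An ICER does so in its numerator. It does not in its denominator if that denominator can pass through zero: the ratio runs to infinity on one side and returns from minus infinity on the other. A bar joining the two end values then covers values that are never reached and omits values that are, including the base case.

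A small denominator is foreseeable here. Both arms deliver the same programme with the same package, the contrast is the learning collaborative alone, and the comparison rests on seven communities.

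Two things are at stake. First, the order of the bars: a more uncertain effect input can be drawn shorter than a less uncertain one. Second, their direction: the worst outcome, in which BHF-LC costs more and achieves less, becomes a negative ICER and appears at the low end of the axis, where a reader expects favourable results.

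**Working it through.** The article states no figure for this point, so there is none to reproduce. The check is of the ratio itself, then of an example, then of how likely a crossing is.

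**General form.** Let the base effect difference be e, the incremental cost dC > 0, and the effect be varied over e ± h, with k = h/e.

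- End ICERs: (dC/e)/(1 − k) and (dC/e)/(1 + k).
- Bar length: (dC/e) × 2k/|1 − k²|.
- A parameter that moves dC by ±p has a bar of (dC/e) × 2p.

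In units of the base ICER, the effect bar is 1.33 at k = 0.5, undefined at k = 1, 2.40 at k = 1.5, 1.33 again at k = 2 and 0.42 at k = 5. Below k = 1 the bar contains the base case and grows with the range. Above k = 1 it excludes the base case and shrinks.

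**Example (all inputs assumed).** Incremental cost $20,000; reductions 0.20 in BHF-LC and 0.15 in BHF-PO. Then e = 0.05 and the base ICER is 20,000/0.05 = $400,000 per unit. Varying the BHF-LC reduction:

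| Change | k | Effect differences | End ICERs | Bar length | Contains $400,000? |
|---|---|---|---|---|---|
| ±20% | 0.8 | 0.01; 0.09 | $2,000,000; $222,222 | $1,777,778 | yes |
| ±25% | 1.0 | 0; 0.10 | undefined; $200,000 | undefined | – |
| ±30% | 1.2 | −0.01; 0.11 | −$2,000,000; $181,818 | $2,181,818 | no |
| ±40% | 1.6 | −0.03; 0.13 | −$666,667; $153,846 | $820,513 | no |

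The crossing comes at a relative change of e/E_LC = 0.05/0.20 = 25%.

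**Does the order change?**

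- Against cost inputs, only far out. Bars for dC ±20%, ±50% and ±100% are $160,000, $400,000 and $800,000, all shorter than the ±40% effect bar. The effect bar drops below a cost bar when k > (1 + √(1 + 4p²))/(2p), which is 5.19 for ±20% and 2.41 for ±50%. In the example these correspond to varying the BHF-LC reduction by about 130% and 60%.
- Against another effect input, sooner. Vary the BHF-PO reduction by ±25% (±0.0375). The differences are 0.0125 and 0.0875, the ICERs $1,600,000 and $228,571, and the bar $1,371,429. The BHF-LC reduction at ±40% moves the effect by ±0.08, about twice as far, yet its bar is $820,513. The order is reversed at k = 1.6.

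**Is a crossing plausible?** The enrolment goal is 12 families × 2 cohorts × 7 communities = 168 families, or 96 against 72. Taking one index child per family, an assumed SD of change of 0.2 to 0.4 and an assumed ICC of 0 to 0.05 with 24 families per community, the 95% half-width is 1.96 × SD × √[(1 + 23 × ICC)(1/96 + 1/72)], which is 0.06 to 0.18. If the range varied were that interval, k would be:

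| True difference | k |
|---|---|
| 0.05 | 1.2–3.6 |
| 0.10 | 0.6–1.8 |
| 0.20 | 0.3–0.9 |

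A crossing is plausible for small differences and does not occur at 0.20 under these assumptions.

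**On a linear scale.** Plotted on incremental effect, the bar length is 2h. In the example it is 0.16 for BHF-LC at ±40% and 0.075 for BHF-PO at ±25%. The order is right, and both bars contain the base value of 0.05.

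**The case against.** A reader might infer that the planned ranking is wrong as it stands. The document does not support that. It states no range, so whether the difference reaches zero is a condition, and a range that keeps the difference positive gives a valid tornado. Nor does a wrong ranking follow as soon as zero is passed: just beyond it the effect bar is very long and still ranks above the cost inputs, which is the right order.

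Four further points can be made in the plan's favour.

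- A condensed article may leave sensitivity ranges to the full protocol or analysis plan. That excuses the missing range. It does not excuse the ranking rule, which the article states and which depends on the range behaving well.
- The section introduces the one-way analysis as serving the cost analysis, and the parameters it lists for the tornado are mostly staffing, session and attendance inputs. Still, it names BMI z-score among the quantities to be varied.
- Effect uncertainty is also shown by 2000 bootstrap samples on the cost-effectiveness plane, where a sign change is visible. This softens the consequence, but the plane does not rank inputs and leaves the tornado rule as it is.
- The Challenges and limitations section says the study does not address decision makers' use of the results, and it is the scenario analyses that are aimed at adopting communities. So the practical harm of a misordered tornado should not be overstated, although the Conclusion does expect the results to assist policy makers and community organizations.

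**Conclusion.** The point holds in conditional form. The plan varies a quantity that enters the ICER through a between-arm difference, and it ranks inputs by ICER bar length. When the half-range exceeds the base difference (k > 1), the bar excludes the base case, puts the unfavourable end on the favourable side of the axis, and shortens as uncertainty grows. Order against another effect input can reverse at about k = 1.6, as the example shows. Order against cost inputs varied by ±50% to ±20% reverses only at about k = 2.4 to 5.2.

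The algebra needs no assumption beyond a positive incremental cost and a positive base difference. The dollar figures and the plausibility ranges rest on assumed cost, effect, SD and ICC, none of which the article gives. The ACER rows, whose denominators are not differences, and the cost-only tornados are not affected.

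**What to change.** For the incremental (ICER) rows, draw and rank the tornado on incremental cost and on incremental effect in separate panels. Show an ICER bar only when the effect difference stays positive over the whole range varied. Leave the ACER and cost-only tornados as planned.

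Incremental net benefit would also give a single linear scale, but only if a value per unit of BMI z-score, or a range of values, is stated. The article gives none: the Data analysis section points to thresholds from earlier economic research, and the Background describes the learning-collaborative studies it cites there in terms of clinician competency and youth mental health.

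The cost is a change of wording and two panels instead of one for the incremental rows. A parameter that moves both cost and effect would appear in both panels. No new data or model runs are needed.

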### Eligibility, recruitment, and allocation

#### Community level

Applying the community engagement approach, the research team and the BHF-CAB disseminated the RFA within and outside their organizations and networks (i.e., applying network weaving strategy) and documented that communities across all 93 counties received the RFA. Eight communities with broad geographic distribution responded to the RFA of which seven rural communities in Nebraska completed a full proposal and were selected as the participating communities for the HEI trial. We then ranked the seven applications in a descending order and allocated the odd-numbered rankings to the (BHF-LC) and the even-numbered rankings to the package-only (BHF-PO) condition [23]. This exercise resulted in four communities in the BHF-LC condition and three communities in the BHF-PO condition. All communities that implement the PWMI will have access to the BHF Online Training Resources and Program Package that includes all of the materials necessary to implement and evaluate the BHF intervention.

Communities assigned to the BHF-PO condition are required to complete a memorandum of agreement (i.e., obtaining formal commitment strategy) to report on the implementation of the PWMI and to use pragmatic evaluation strategies for reach and effectiveness outcomes and to provide de-identified program data for baseline, 6, and 12 months. These communities will also have technical support as needed related to package function, but no other facilitation. Communities allocated to the BHF-LC condition will participate in LC training lessons with additional embedded implementation support activities with a goal to (1) develop local strategies to screen and engage families through the BMI Reporter in schools or clinical screening and referral, (2) increase implementation fidelity, and (3) plan for sustainability.

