### Overview of economic evaluation

This protocol has been reported in line with the Consolidated Health Economic Evaluation Reporting Standards (CHEERS) checklist [28] (see Supplementary File 1: CHEERS Checklist).

The economic evaluation of the HEI trial is two-fold. First is to conduct a cost and cost-effectiveness analysis of the fund and contract dissemination strategy for the BHF adoption, the BHF Online Training Resources and Program Package relative to BHF adoption and implementation, and the BHF-LC implementation strategy for promoting BHF adoption, implementation fidelity, and sustainability for the duration of the trial (12 months). The second is to conduct a cost and cost-effectiveness analysis of the BHF intervention. The CEA will be conducted from an implementing community [29] and limited societal perspective (i.e., including only productivity loss of participants due to the participation in the BHF program). The perspective of implementing community would include costs of time spent on planning, training, recruitment, delivering, and post-session follow-up, resources used, communication with the research team and BHF participants, and opportunity costs of community facilitators. Moreover, we will include the time and costs of the research team for providing training, facilitation, and technical assistance. Costs associated with research administration, data collection, and trial outcome assessment will be excluded. All costs will be categorized as labor and non-labor costs (e.g., space, supplies, or information technology) and expressed as US $2022. The unit of analysis for the economic evaluation is the 7 communities consisting of approximately 21–28 community facilitators who will be provided with BHF Online Training Resources and Program Package with or without a LC implementation strategy to implement and deliver the BHF intervention. The time horizon of the within-trial CEA will be across a 15-month period of time (first 3 months for preparation, and later 12 months for BHF intervention), to incorporate sufficient time to complete the whole implementation process of one BHF cohort, initiating from preparation, training, recruitment, and program delivery to post-intervention follow-up. This differs from the primary clinical effectiveness time horizon of 6 months. Costs and benefits will not be discounted due to a short duration.

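### The bootstrap of cost-effect pairs names no resampling unit, and with 7 communities (4 vs 3) its nominal 95% interval for incremental cost is too narrow whether a pair is a family or a community

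*Protocol article*

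**What the plan says.** All references are to the protocol article.

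- **Allocation** (Community level): the investigators "ranked the seven applications in a descending order and allocated the odd-numbered rankings to the (BHF-LC") arm and the even ranks to package only. "This exercise resulted in four communities in the BHF-LC condition and three communities in the BHF-PO condition".
- **Unit** (Overview of economic evaluation): "The unit of analysis for the economic evaluation is the 7 communities consisting of approximately 21–28 community facilitators".
- **Bootstrap** (Sensitivity analysis): "2000 random samples of cost-effect pairs will be selected with replacement from the original trial dataset". Its purpose is joint uncertainty, with a 95% confidence interval as the example, "for the incremental costs and incremental effects (i.e., BMI *z*-score reduction) between BHF-LC and BHF-PO conditions". Neither clustering nor arm is mentioned in the draw.
- **Other sensitivity analysis** (same section): "one-way deterministic sensitivity analysis (DSA) [35] for the cost analysis of D&I strategies and BHF program training, recruitment and delivery", varying "key unit costs, cost components, and outcome measures (i.e., BMI" z-score), with tornado diagrams and scenario analyses.
- **Aims** (Study design): "the primary aim is to determine if the LC communities document better D&I outcomes", namely reach, adoption, implementation and sustainability. BHF effectiveness is the secondary aim.
- **Limitation** (Challenges and limitations): the study may be underpowered because of 21–28 facilitators. Clustering and the validity of intervals are not discussed.

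**The concern.** The BMI z-score is measured on children, so a family is a natural candidate for the pair. But the learning collaborative is assigned to communities, and facilitator time for training, recruitment, preparation and delivery is spent per cohort or community. A family's cost is then largely its share of a community total. Resampling families would count that one total as many separate observations. Resampling communities respects the design but leaves four and three values to draw from, too few for a percentile interval to behave well.

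At stake are the incremental cost-effectiveness plane and its 95% interval, which would show more precision than seven communities can give. Separately, the Table 1 ratios for reach, cohorts initiated, fidelity and maintenance, which carry the primary aim, have no measure of sampling variation at all, yet Data analysis compares ratios with thresholds.

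**Working it through.** **Inputs from the article.** Odd and even ranks of 7 give 4 and 3 communities, as stated. Facilitators per community: 21/7 = 3 to 28/7 = 4. Families (Individual level): 12 per cohort × 2 cohorts = 24 per community, or 7 × 24 = 168 in all. The economic time horizon is set to cover one cohort, so 12 per community is an equally fair cluster size. The stated total of 420–672 equals 7 × 2 × 30 to 7 × 2 × 48, a count of individuals rather than of families. The article gives no ICC and no interval width, so the ICC below is assumed.

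**Reading 1: pairs are families.** Design effect = 1 + (m − 1) × ICC; the naive SE is too small by its square root.

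| ICC | Design effect, m = 12 | SE factor | Design effect, m = 24 | SE factor |
|---|---|---|---|---|
| 0.01 | 1.11 | 1.05 | 1.23 | 1.11 |
| 0.05 | 1.55 | 1.24 | 2.15 | 1.47 |
| 0.10 | 2.10 | 1.45 | 3.30 | 1.82 |
| 1 (cost fully shared) | 12 | 3.46 | 24 | 4.90 |

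Actual coverage of the nominal 95% percentile interval was simulated with 1,500 trials, 2,000 resamples each, 4 vs 3 communities, normal data and resampling of families within arm:

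| ICC | m = 12 | m = 24 |
|---|---|---|
| 0 | 94% | 94% |
| 0.01 | 92% | 93% |
| 0.05 | 86% | 81% |
| 0.10 | 81% | 70% |
| 1 | 34% | 25% |

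Monte Carlo standard error near 80% is √(0.8 × 0.2/1500) ≈ 1 point. A repeat simulation gave 90–93%, 83–87%, 70–79% and 27–31% at ICC 0.01, 0.05, 0.10 and 1, so single figures are good to about 3 points. The ranges in the verdict span both.

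**Reading 2: pairs are communities, resampled within arm.** Distinct resamples: C(7,4) × C(5,3) = 35 × 10 = 350. A package-only resample contains a single community with probability 3/27 = 11%.

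The expected bootstrap variance of the difference, in units of the between-community variance of means, is (3/4)/4 + (2/3)/3 = 0.410. The true value is 1/4 + 1/3 = 0.583. The SE is therefore too small by √(0.410/0.583) = 0.84, and the interval also uses roughly 1.96 where t on 5 df needs 2.57, a factor of 0.76. Together that is 0.84 × 0.76 ≈ 0.64 of the required width; the simulation gave about 60% (2.37 against 3.93 SD at ICC 1). Simulated coverage is about 82% (81–85%) at every ICC.

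If the draw is not stratified by arm, one arm is empty with probability (4/7)^7 + (3/7)^7 = 2.3%, and no increment can be formed.

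**Alternative.** A t interval on the seven community means has 4 + 3 − 2 = 5 df and covers about 95%. At ICC 0.05 and m = 24 its width is 1.11 SD, against 0.60 SD for the family-level bootstrap.

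**The case against.** A reader might infer that the plan resamples families as if they were independent. The article does not say so. It names no resampling unit, and its only declared unit of analysis is the community. That objection stands, so the point rests on both readings.

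It can also be said that resampling level, strata and interval type belong in the analysis plan. Silence on them would indeed be no finding. But the method, the number of draws, the target and the interval level are fixed, and the percentile version falls short under either unit. The article does not name the interval type, and coverage of other bootstrap intervals was not computed.

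The size for the BMI effect depends on an ICC that the documents do not give; at 0.01 or below coverage is near nominal. The 25–34% figure is the extreme for a cost fully shared within the community. Under the limited societal perspective, family time and travel vary by family. Learning sessions run by the research team are largely common to the whole arm, and no resampling can show uncertainty in that part.

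A reader might also infer that the primary ratios would be reported as near-certain, or with cost variation only. The documents do not support this. The trial is called a pilot, low power is conceded, and the deterministic analysis has an open-ended parameter list that includes session number and attendance time. Still, none of that measures sampling variation.

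Finally, a t interval on 5 df is not credible for cohorts initiated or third cohorts, which are tiny counts that may not vary within an arm. That stands and limits the remedy. Separate intervals also do not give the joint uncertainty that the plane is meant to show.

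**Conclusion.** The concern holds in a limited form. The bootstrap's unit and strata are not fixed, and the percentile interval for incremental cost is too narrow on either reading: about 25–34% coverage for a fully shared cost if pairs are families, about 82% if pairs are communities. For the BMI effect under family resampling, coverage is about 90–93%, 81–87% and 70–81% at ICC 0.01, 0.05 and 0.10.

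These figures assume normal data, equal community sizes of 12 or 24 families, an assumed ICC, and communities exchangeable between arms although allocation alternated by rank. The lack of a sampling interval for the primary implementation ratios follows from the text and needs no assumption. This is a should-fix: the bootstrap is a sensitivity analysis for the secondary aim of a pilot.

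**What to change.** - In Sensitivity analysis, name the community as the unit. Base the intervals for incremental cost and BMI z-score effect on community means with a t reference on 5 df, or on a mixed model with community random effects and small-sample degrees of freedom.
- If the cost-effectiveness plane is kept, resample whole communities within arm and label it descriptive.
- For reach and fidelity, report community-level values with the same interval. For cohorts initiated and third-cohort maintenance, list the seven community values without an interval.
- In Challenges and limitations, state the sample-size limit as 7 communities rather than 21–28 facilitators.

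The cost is a change of wording, a little code and wider intervals. No new data are needed.
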